### Power calculation

We estimated the number of participants to be included in the trial based on a statistical power analysis of the primary outcome using clustered parallel groups with before-and-after measures to determine the design effect. The power calculation was based on data from a larger sample (*N* = 167) of childcare workers in Copenhagen in a previous trial (ISRCTN10928313) [51]. In this sample, work time spent with a heart rate reserve (HRR) ≥60% was, on average, 1.24 min/day with a standard deviation (SD) between subjects of 2.90. The power calculation was done after processing data according to the principles of compositional data analysis (CoDA) [52, 53], where work time spent at HRR ≥60% is expressed relative to time spent at HRR < 60% using isometric log-ratios (ilr) [54–56]. Expressed as an ilr, the average relative work time spent at HRR ≥60% was − 4.35 (SD = 1.10).

Based on these transformed data, we will need an estimated total of 132 participants (corresponding to approximately 14 childcare institution clusters shared between the intervention and wait-list groups) to be able to detect (at *p* < 0.05) a 5 min/day increase in relative work time spent at HRR ≥60% with a power of 0.80, an estimated intra-cluster correlation coefficient (ICC) of 0.05, a fixed cluster size of 10, and an assumed drop-out rate of 30%.

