### Primary and secondary outcomes

Differences between the intervention and the control groups in changes from baseline to 10-week follow-up will be evaluated for all primary and secondary outcomes. The primary outcome is the relative work time spent in MVPA, as determined by either heart rate (i.e. ≥60% of heart rate reserve) or accelerometer recordings (i.e. fast walking (≥130 steps/ minute), running, or stair climbing).

Furthermore, the study has four secondary outcomes: i) cardiorespiratory fitness, ii) resting heart rate during sleep, iii) perceived need for recovery; and iv) self-reported productivity. Figure 4 shows the SPIRIT schedule of enrolment, interventions, and assessments [22].

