### Strengths and limitations of the study

A methodological strength of the study is the use of a cluster randomised design, which minimises the risk of contamination within and between institutions in the intervention and control groups. Another methodological strength is the application of a systematic participatory approach involving the end users throughout the entire process. We will collect experiences and information during the process of developing and tailoring the intervention, and this can likely benefit the present as well as future studies. Even the use of wearable accelerometers and heart rate monitors for measuring the primary outcomes is a strength. By using wearable sensors rather than self-reported methods to record the primary outcome, bias introduced by self-reports, e.g. due to lack of blinding of participants or inaccurate perception [60], is considered minimal.

In addition, utilizing CoDA is a strength of this study, since it allows the co-dependency between work time spent in different behaviour types (sedentary behaviour; light physical activity; MVPA) to be taken into account. Thus, the use of CoDA represents an approach that gives a better understanding of the potential effect of an intervention from a whole-workday perspective than if each behaviour is analysed as an independent factor [56, 61]. Furthermore, conducting a process evaluation is a strength of this study. The process evaluation provides an opportunity for thoroughly evaluating the implementation of the intervention and identify why the intervention may or may not be effective.

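### The stated 80% power is for work time at HRR ≥60% alone, not for the declared primary outcome, which also counts accelerometer-defined MVPA

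*Protocol article*

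**What the plan says.** Primary and secondary outcomes (protocol article) names one primary outcome, the share of work time in MVPA, "as determined by either heart rate (i.e. ≥60% of heart rate reserve) or accelerometer recordings". The accelerometer criterion is "fast walking (≥130 steps/ minute), running, or stair climbing".

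The Power calculation section says the number of participants was "based on a statistical power analysis of the primary outcome". The planning data come from 167 childcare workers in an earlier trial, and the variable is the heart-rate criterion only: "work time spent at HRR ≥60% is expressed relative to time spent at HRR < 60% using isometric log-ratios". Its mean was "1.24 min/day with a standard deviation (SD) between subjects of 2.90". On the ilr scale this is −4.35 (SD 1.10). From these values the section derives 132 participants in about 14 institutions to detect "a 5 min/day increase in relative work time spent at HRR ≥60% with a power of 0.80", with ICC 0.05, cluster size 10 and 30% drop-out.

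The Power calculation section does not mention accelerometer-defined time. Nowhere does the article say that the heart-rate figures stand in for the wider measure.

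**The concern.** The article fixes both the primary outcome and the basis for the sample size, and the two are different variables. This is not a detail that a condensed article may leave to a fuller document, because both statements are made here and they disagree.

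The mismatch matters because of the log-ratio scale. If a minute counts when either criterion is met, adding accelerometer time can only raise the baseline minutes. A fixed gain in minutes is then a smaller shift in log-ratio units. The SD changes as well, probably downward, since the heart-rate variable is very sparse (SD more than twice the mean). The net effect on power cannot be read off the heart-rate calculation.

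At stake is whether 0.80 and 5 min/day describe the comparison on which the trial will be judged. The same outcome is also the effect term in the cost-effectiveness ratio (Economic evaluation).

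**Working it through.** **1. The two definitions side by side**

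| | Primary outcome | Power calculation |
|---|---|---|
| Heart rate ≥60% HRR | counted | counted |
| Fast walking, running, stair climbing | counted | not mentioned |
| Mean, SD, target effect | none given | 1.24 min/day, SD 2.90; ilr −4.35, SD 1.10; +5 min/day |

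**2. The plan's own figure**

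Formula: n per arm = 2 × [(1.96 + 0.84) × SD / δ]², times the design effect 1 + 9 × 0.05 = 1.45, divided by 0.70 for drop-out. Two-sided 5% is assumed. Workday length T and the before-after correlation are not given.

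With ilr(x) = √½ × ln[x / (T − x)] and T = 420 min assumed, ilr(1.24) = −4.12 and ilr(6.24) = −2.97, so δ = 1.15.

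- Variance SD² (post-only, or change score with correlation 0.5): n = 2 × (2.80 × 1.10 / 1.15)² = 14.3, rounded up to 15. The total is 2 × 15 × 1.45 / 0.70 = 62.1, so 63.
- Variance 2 × SD² (change score, correlation 0): n = 29. The total is 2 × 29 × 1.45 / 0.70 = 120.1, so 121.
- Target read as a rise to 5 min rather than by 5 min, correlation 0: totals of 75 to 162 over workdays of 300 to 582 min and both choices of baseline (1.24 min, or the value implied by ilr −4.35).

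Back-solving: 132 × 0.70 = 92.4 analysed, and 92.4 / 1.45 / 2 = 31.9 effective per arm. The detectable shift is 2.80 × 1.10 × √(2/31.9) = 0.77 ilr.

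So 132 can be neither confirmed nor called wrong without T and the correlation. The point does not depend on it.

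**3. How +5 min/day changes with the baseline**

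Shift = ilr(b + 5) − ilr(b), T = 420 assumed. For example, from b = 10: −2.33 − (−2.63) = 0.30. The baselines above 1.24 are assumptions.

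| Baseline b (min/day) | Shift (ilr) |
|---|---|
| 1.24 (heart rate only, from the article) | 1.15 |
| 3 | 0.70 |
| 5 | 0.50 |
| 10 | 0.30 |
| 20 | 0.17 |

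A 450-minute day changes these values by 0.001 or less.

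**4. What that could mean for power (illustration only)**

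Assumed: 92.4 analysed in 14 clusters, or 6.6 per cluster, so the design effect is 1 + 5.6 × 0.05 = 1.28. SE = SD × √(4 × 1.28 / 92.4) = 0.235 × SD, with a noncentral t on 12 df and the single-time-point variance.

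| Baseline | Power, SD 1.10 | Power, SD 0.6 |
|---|---|---|
| 1.24 | 0.98 | about 1.00 |
| 3 | 0.70 | 0.995 |
| 5 | 0.43 | 0.90 |
| 10 | 0.18 | 0.49 |
| 20 | 0.09 | 0.19 |

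SD 1.10 is the heart-rate value carried over. SD 0.6 is assumed, for a less sparse measure. The table spans both sides of 0.80.

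**The case against.** The strongest reply is that the harm is assumed and not shown. Four parts of it stand.

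- The Background says childcare workers spend little work time in MVPA, which points to the low end of the baselines. At 3 to 5 min/day with SD 0.6, power is 0.90 or more.
- The 5-minute target was set for heart-rate time. If minutes meeting only the accelerometer criterion also count, the expected gain may be larger. A gain of 10 min/day from a baseline of 5 is a shift of 0.79 ilr, with power 0.80 even at SD 1.10.
- The article plans on before-and-after measures, and the illustration does not use them. With an assumed correlation of 0.7 and baseline adjustment, power at SD 1.10 rises from 0.70 to 0.94 (baseline 3) and from 0.43 to 0.70 (baseline 5). Change scores with a low correlation would lower it.
- The illustration gives 0.98 for the variable that was powered, where the article states 0.80. Its absolute percentages are therefore not this trial's power.

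Three stronger readings are tempting, and the article does not support them.

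- *The trial is underpowered.* The inputs needed to say so are absent.
- *There are two competing primary outcomes and an inflated type I error.* The Abstract and the outcomes section name one primary outcome in the singular. The either/or wording reads naturally as a minute counting if either criterion is met, and no section plans two tests. The plural in the Strengths and limitations section is loose wording, since its next sentence uses the singular.
- *The composition in that section ("sedentary behaviour; light physical activity; MVPA") contradicts the two-part split in the power calculation.* It describes the general merit of compositional analysis and does not set the primary contrast. MVPA against remaining work time fits the outcome definition.

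None of this removes the mismatch. The power is stated for the primary outcome but computed for one component, and the article does not say so.

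**Conclusion.** The point holds as a mismatch between the declared outcome and the variable that was powered. The figures of 132 participants, power 0.80 and 5 min/day apply to work time at HRR ≥60%, and they are not shown for MVPA by heart rate or accelerometer.

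The size of the mismatch can be given only as non-transferability: the same 5 min/day is 1.15 ilr units from the heart-rate baseline and 0.70, 0.50 or 0.30 from baselines of 3, 5 or 10 min/day. These shifts rest on the assumed 420-minute day, to which they are insensitive, and on assumed baselines. Whether the power for the combined outcome is above or below 0.80 is open.

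Confidence is high on the textual mismatch. No loss of power is claimed. This should be fixed, but it does not threaten the design.

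**What to change.** Before any analysis by arm, do one of the following.

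(a) Name work time at HRR ≥60%, in the two-part ilr, as the single primary variable, and make accelerometer-defined MVPA supportive. The existing power statement then belongs to the primary outcome.

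(b) Keep the combined outcome. State that a minute counts if either criterion is met, and fix the ilr coordinate as MVPA against remaining work time. Then restate the power and detectable difference for that variable, using existing data or baseline data pooled over arms and blinded. Give the mean, SD, ICC and target effect used.

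Under either option, report the workday length and before-after correlation behind the calculation, so that the figure can be checked.

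The cost is wording in the protocol or analysis plan and, under (b), one rerun of the power calculation. Enrolment and randomisation are unchanged. The downside of (b) is that the restated power may be less favourable. The downside of (a) is that minutes meeting only the accelerometer criterion no longer count toward the primary outcome.

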### Statistical analysis

Evaluation of intervention effectiveness on the primary and secondary outcomes as well as the cost-effectiveness will be based on multilevel models, taking into account that the study design implies repeated measurements within each participant [57]. Conclusions about the effectiveness of the intervention with respect to the primary and secondary outcomes will be based on the group effect and its 95% confidence interval. The 95% confidence intervals for the incremental cost-effectiveness ratio will be estimated using bootstrapping (1000 bootstrap samples with replacement) [58]. All analyses will be performed according to the intention-to-treat principle [59]. Potential confounding factors (e.g. baseline differences between the intervention and control group in factors like age and BMI) will be adjusted for in the statistical analyses.

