### Study design

Figure 1 provides an overview of the study design. The study will use a cluster-randomised design with a usual-practice wait-list control group. As the study is an organisational intervention in a work place setting, individual randomisation is neither possible nor appropriate [25]. Thus, each participating institution will form a cluster. A wait-list design (offering the intervention to the intervention and, eventually, even to the control groups) was chosen in an attempt to minimise any potential lack of commitment from an institution acting as control [26]. Thus, we will randomly assign the participating childcare institutions to, i) the intervention group immediately receiving the intervention after the baseline measurements or, ii) the control group continuing usual practice for 10 weeks after the baseline measurements and then performing the intervention. Each intervention period will last 10 weeks. After the 10 weeks intervention for the intervention group, they will be encouraged to continue with Goldilocks-games without further support from the research team.

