### Randomisation and blinding

Cluster-randomisation will be used with each childcare institution constituting a cluster, in order to avoid contamination within an institution between participating and non-participating workers. Participating childcare institutions will be randomised to either intervention or usual practice (i.e. wait-list control) arms of the trial. This randomisation will be conducted upon enrolment of each participating childcare institution into the study. The randomisation sequence has been developed using the statistical software R [27].

Because of the time needed for the childcare institutions to plan their participation in the trial, we need to inform them about their allocation to intervention or control group before the baseline data collection. Moreover, due to the nature of the trial, it will not be possible to blind neither the researchers nor the participating employees as regards whether a particular institution is subject to the intervention or not. However, allocation concealment will be maintained throughout the study, and all researchers conducting the randomisation, statistical analysis, and evaluation will be blinded.

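### The analysis section names repeated measurements within participants but not the randomised institution; a model fitted as literally described would give 95% confidence intervals that are too narrow

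*Protocol article*

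**What the plan says.** The protocol article is clear that the design is clustered. Under Study design, "each participating institution will form a cluster", and Randomisation and blinding repeats it: "Cluster-randomisation will be used with each childcare institution constituting a cluster". The Power calculation section derives a design effect for clustered groups measured before and after, with "an estimated intra-cluster correlation coefficient (ICC) of 0.05, a fixed cluster size of 10, and an assumed drop-out rate of 30"%. It arrives at 132 participants in about 14 institutions.

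The section on primary and secondary outcomes sets the contrast: "Differences between the intervention and the control groups in changes from baseline to 10-week follow-up will be evaluated for all primary and secondary outcomes".

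Only the Statistical analysis section describes the effectiveness model. It names multilevel models for effectiveness and cost-effectiveness and describes them as "taking into account that the study design implies repeated measurements within each participant". It adds that conclusions on the primary and secondary outcomes "will be based on the group effect and its 95% confidence interval". It mentions no institution level, intra-cluster correlation or cluster-robust variance. The interval for the cost-effectiveness ratio comes from 1000 bootstrap samples, and the section does not say what unit is resampled.

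**The concern.** The sentence does more than leave the model open. It names a dependence that the design implies, and leaves out the one created by randomising institutions. An analyst who follows it literally would fit visits within participants. That treats about 92 workers (132 × 0.7 = 92.4) as independent, when 14 institutions were allocated.

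In a contrast of change, a participant effect absorbs every stable difference, including stable differences between institutions. It does not absorb change that the workers of one institution share. The protocol gives reason to expect such change. Games and action plans are developed separately at each institution (Intervention content), the local management and staff representatives tailor the process (Intervention), and interviews are planned to pick up local events that could alter implementation or effect (Process evaluation).

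At stake is the validity of the interval that carries every primary and secondary conclusion. The trial would also allow for clustering when setting its size and then not allow for it in the analysis.

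**Working it through.** **The plan's own figure.** The total of 132 could not be reproduced, because the difference on the log-ratio scale, the workday length and the baseline-to-follow-up correlation are not given. Using SD 1.10, two-sided 5%, 80% power, design effect 1.45 and 30% drop-out, with workdays of 360 to 480 minutes and correlations of 0 to 0.5 assumed, totals ran from 32 to 123. The step from participants to institutions is consistent: 132 / 10 = 13.2, rounded up to 14. Nothing below depends on how 132 was obtained.

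**Inputs.** ICC 0.05, cluster size 10, drop-out 30%, 132 participants and about 14 institutions (Power calculation). Assumed: an equal split between arms, a two-sided 5% level in line with the 95% interval, and, in step 1, that the ICC applies to the change.

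**Step 1: error if institution is ignored.** The design effect is DE = 1 + (m − 1) × ICC. The type I error is 2 × [1 − Φ(1.96 / √DE)]. The standard error is too small by 1 − 1/√DE.

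- m = 132 × 0.7 / 14 = 6.6: DE = 1 + 5.6 × 0.05 = 1.28. Type I error is 8.3%, and the standard error is 12% too small.
- m = 10: DE = 1 + 9 × 0.05 = 1.45. Type I error is 10.4%, and the standard error is 17% too small.

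**Step 2: what if the ICC refers to levels?** The Power calculation section does not say whether 0.05 refers to a single visit or to the change. Let ρ be the single-visit ICC, c the cluster autocorrelation (how stable the institution effect is between visits) and r the within-person correlation. Then

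ICC of change = 2ρ(1 − c) / [2ρ(1 − c) + 2(1 − ρ)(1 − r)].

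With ρ = 0.05, c = 0.8 and r = 0.5 this is 0.02 / (0.02 + 0.95) = 0.0206. With r held at 0.5 (c and r are assumptions):

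| c | ICC of change | DE, error at m = 7 | DE, error at m = 10 |
|---|---|---|---|
| 1 | 0 | 1.00, 5.0% | 1.00, 5.0% |
| 0.8 | 0.0206 | 1.124, 6.5% | 1.186, 7.2% |
| 0.5 | 0.05 | 1.30, 8.6% | 1.45, 10.4% |
| 0 | 0.0952 | 1.571, 11.8% | 1.857, 15.0% |

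Here m = 7 is a planned cluster of 10 after 30% drop-out. The nominal 5% holds only in the first row, where institution effects do not move at all.

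**Step 3: simulation.** With 14 institutions and an ICC of change of 0.05, an analysis ignoring institution rejected a true null in 8.4% of runs at 7 per institution and 10.4% at 10. A cluster-level t-test on 14 − 2 = 12 degrees of freedom rejected in 5.0 to 5.1%.

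**Step 4: width of a valid interval.** The critical t on 12 degrees of freedom is 2.179. Relative to the model ignoring institution, the interval widens by the factor (2.179 / 1.96) × √DE:

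- m = 6.6: 1.112 × 1.131 = 1.26.
- m = 10: 1.112 × 1.204 = 1.34.

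**The case against.** The strongest reply is that the text does not exclude institution. It does not say that within-participant dependence is the only kind handled, multilevel models can hold three levels, and the authors plainly know that the design is clustered. A journal article may also leave the full random-effects structure and the degrees-of-freedom method to an analysis plan that is not shown. This stands to the extent that omission is not established, and the error rates above are conditional on it. It does not remove the point. The sentence itself says which dependence is taken into account, and what it names does not match the design or the sample-size basis. The unit of analysis in a cluster-randomised trial is not a minor detail.

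A second reply is that the contrast is a change, so institution effects may cancel. This stands in part: they cancel if fully stable, and an autocorrelation of 0.8 brings the error down to 6.5 to 7.2%. The protocol's emphasis on local tailoring makes full stability hard to assume.

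A reader might also infer that the plan uses normal-theory tests that are too liberal for 14 clusters. The section names no reference distribution, so that criticism has no basis in the text. The 12 degrees of freedom matter only for specifying the corrected analysis. Nor is it right to refer the naive statistic to a t distribution on 12 degrees of freedom, which would give 10.9% and 13.0%. The naive standard error is estimated from some 90 or more workers, and the simulation agrees with the normal-reference figures.

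**Conclusion.** The point holds in conditional form. The stated model covers repeated measurements within participants and is silent on the randomised unit. Fitted as literally described, it gives 95% intervals that are too narrow: type I error of about 8.3 to 10.4% if the protocol's ICC of 0.05 applies to the change, about 6.5 to 7.2% under the assumed autocorrelation of 0.8 and within-person correlation of 0.5, and 5% only if institution effects are fully stable.

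A reader might go further and conclude that the trial will be analysed without institution and that its error rate does exceed 5%. The document does not support that: it neither includes nor excludes an institution level, and it does not say what the ICC of 0.05 describes. The silence still needs correcting, because this one sentence governs every primary and secondary conclusion.

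**What to change.** State in the Statistical analysis section that the analysis of all primary and secondary outcomes accounts for institution as the randomised unit in the change contrast. Any of these would serve:

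- a baseline-adjusted model of the 10-week value with a random institution intercept;
- a repeated-measures model with participants nested in institutions and an institution-by-time effect;
- a cluster-level analysis.

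In the repeated-measures form, a time-constant institution intercept alone would not be enough, since it does not capture shared change.

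Add a small-sample reference suited to about 14 clusters (about 12 degrees of freedom, critical t about 2.18), and say that the cost-effectiveness bootstrap resamples institutions.

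This needs no extra data or participants. The cost is precision: at ICC 0.05 with 12 degrees of freedom the interval is roughly 26 to 34% wider than that of a model ignoring institution. If institution was always meant to be in the model, the change is one of wording.

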### Economic evaluation

The economic evaluation aims to determine the cost-effectiveness of the intervention in terms of cost (from the employer’s perspective) per increment in work time spent in MVPA. Costs of the intervention will include costs related to implementation and operation, specifically:

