#### Staff time

Participation in intervention activities for workers (workshops, and kick-off meeting for the project), and Trio (workshops, kick-off meeting for the project, and time spent on planning the logistics of implementing the intervention) will be assessed based on registration of attendance. Costs for participants and supervisors will subsequently be estimated based on their average yearly gross salaries, including overhead.

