#### Consumables

Materials, such as printouts and posters, as well as fruit/snacks/coffee consumed at meetings will be noted. Costs will be valued using invoices.

For the control group, only costs related to participation in the joint kick-off meeting will be included.

The total intervention costs for the employer will be estimated and compared between the intervention and control group. The incremental cost-effectiveness ratio will be calculated by dividing the mean difference in costs (incremental cost) between both groups by the difference in effects (incremental effect) on the primary outcome measure.

In addition, sickness absence will be measured by questionnaire from the participants in the control and intervention groups at baseline and 10-week follow-up.

Costs associated with absenteeism will be estimated using the Friction-Cost approach [48]. A friction period of 4 weeks will be assumed, as the Danish social security system takes over costs after 4 weeks of sickness absence. Furthermore, an appropriate elasticity factor will be used. Health-related productivity losses will be valued using gross yearly salaries of the participants converted to a daily cost based on assumed numbers of working days per year.

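### The cost-effectiveness analysis names neither institution as a model level nor institutions as the bootstrap unit; resampling workers would make the ICER interval modestly too narrow

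*Protocol article*

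**What the plan says.** The Randomisation and blinding section sets the unit of allocation: "Cluster-randomisation will be used with each childcare institution constituting a cluster". The Power calculation section plans for about 14 institutions, a cluster size of 10, an ICC of 0.05 and 30% drop-out.

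The Statistical analysis section then says that effectiveness "as well as the cost-effectiveness will be based on multilevel models, taking into account that the study design implies repeated measurements within each participant". No other source of dependence is named there. On the economic interval it says "The 95% confidence intervals for the incremental cost-effectiveness ratio will be estimated using bootstrapping (1000 bootstrap samples with replacement"). The resampling unit and the type of interval are not given.

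The Economic evaluation section defines the target as "cost (from the employer’s perspective) per increment in work time spent in MVPA". The ratio is formed, under Consumables, by "dividing the mean difference in costs (incremental cost) between both groups by the difference in effects (incremental effect) on the primary outcome measure". Costs come from several sources. Staff time "will be assessed based on registration of attendance", consultant time is the hours that the consultants report, and consumables are taken from invoices. Control institutions carry only the cost of the joint kick-off meeting.

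The Primary and secondary outcomes section states: "The primary outcome is the relative work time spent in MVPA". In the Power calculation section, "work time spent at HRR ≥60% is expressed relative to time spent at HRR < 60% using isometric log-ratios (ilr").

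**The concern.** A bootstrap interval takes its spread from the units that are resampled. If workers are drawn singly from a trial that allocated institutions, between-institution variation is largely lost from that spread, whatever model is fitted inside each resample.

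Two components are affected. The effect is clustered by the protocol's own assumption (ICC 0.05). Part of the cost is also clustered: consultant hours and consumables arise per workshop or visit and reach workers only by allocation. The text names one dependence, within-worker repetition, and omits the one created by the randomisation. An analyst who follows it as written could therefore report an employer's cost per unit of MVPA with more certainty than about 14 institutions can support.

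Two smaller matters affect how the ratio is read. The route from the modelled primary outcome to a denominator in work time is not spelled out. A confidence interval for a ratio is also hard to interpret when the resampled effect differences fall on both sides of zero.

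**Working it through.** The protocol gives no numerical ICER or interval, so there is no figure to reproduce. The inputs below come from the Power calculation section unless marked as assumed.

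**1. Effect standard error.** Design effect = 1 + (m − 1) × ICC, with ICC = 0.05.

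- m = 10 (planned size): 1 + 9 × 0.05 = 1.45; √1.45 = 1.20.
- m = 7 (10 less 30% drop-out): 1 + 6 × 0.05 = 1.30; √1.30 = 1.14.
- m = 6.6 (132 × 0.70 / 14): 1 + 5.6 × 0.05 = 1.28; √1.28 = 1.13.

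The worker-level standard error is thus too small by a factor of 1.13 to 1.20. A nominal 95% interval for the effect would cover about 90% (m = 10) or 91% (m = 7).

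**2. Cost standard error alone.** If cost were fully constant within an institution (cost ICC = 1, an assumed extreme), the design effect equals m. The factor is then √7 = 2.6 to √10 = 3.2.

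**3. Why step 2 does not carry over to the ICER.** To first order, the squared relative standard error of a ratio is the sum of those of cost and effect. Assume 7 institutions per arm, cost coefficient of variation 30%, cost ICC = 1, control costs negligible, and an effect at the planned strength of 1.96 + 0.84 = 2.80 standard errors. With m = 10:

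- Institution level: (1/2.80)² + 0.30²/7 = 0.1276 + 0.0129 = 0.1404.
- Worker level: 0.1276/1.45 + 0.30²/70 = 0.0880 + 0.0013 = 0.0893.
- Ratio of standard errors: √(0.1404/0.0893) = 1.25.

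The effect term dominates, so even an extreme cost ICC moves the whole interval little.

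**4. Simulation.** Worker-level and institution-level percentile bootstraps of an ICER were compared. The settings were 7 institutions per arm, 1000 resamples, 400 trials per scenario, m = 7 or 10, cost coefficient of variation 30%, and two assumed effect sizes (1.0 and 0.77).

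| Effect ICC | Cost ICC | Institution-level width ÷ worker-level width |
|---|---|---|
| 0.05 | 0.05 | 1.04 to 1.18 |
| 0.05 | 0.5 | 1.12 to 1.19 |
| 0.05 | 1 | 1.08 to 1.24 |
| 0.20 | 1 | 1.80 to 2.19 |

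At effect ICC 0.05, coverage ranged from 84% to 97% for worker-level and from 90% to 95% for institution-level resampling. Monte Carlo standard error is about √(0.9 × 0.1/400) = 1.5 points. With 7 institutions per arm, the institution-level bootstrap can itself fall somewhat short of 95%.

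**5. Scale.** If the denominator were an ilr, where ilr = ln(x/(T − x))/√2, one unit multiplies x/(T − x) by e^√2 = 4.11. With T = 444 min (assumed), that adds about 1.6 min/day from a baseline of 0.5 min, 3.8 from 1.24 min and 12 from 4 min. Cost per ilr unit therefore has no fixed equivalent in minutes.

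**6. Crossing zero.** If the true effect were half the planned one, it would lie 2.80/2 = 1.4 standard errors from zero. About Φ(−1.4) = 8% of resampled differences would then be negative, which exceeds the 2.5% in each tail.

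**The case against.** The best defence is that the text does not say workers are resampled. Drawing whole institutions is also sampling with replacement, and the cited bootstrap reference is not available here. The authors clearly know the design is clustered: they use an ICC and a design effect for the sample size, and they state multilevel models. A journal article may also leave the resampling unit to a fuller plan. This stands in part. A worker-level bootstrap is one reading of the text, not a stated method. But the section does describe a dependence structure, and the one it describes leaves out the randomised unit. That is more than an omitted detail.

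A reader might infer several stronger claims, which the documents do not support.

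- **That the interval is far too narrow.** The factor of 2.6 to 3.2 applies to the cost standard error alone at an assumed cost ICC of 1. A gap of about two-fold in the ICER interval needed an effect ICC of 0.20, which the protocol does not assume.
- **That all costs arise per institution.** Staff time is based on attendance and can differ between colleagues. Absenteeism costs, if they enter the ratio, come from individual questionnaires.
- **That the ratio is on the wrong scale.** The Economic evaluation section states work time in MVPA. The ilr is specified for the power calculation, and compositional analysis is otherwise praised in general terms in the Discussion. Nothing says that the ICER denominator is an ilr, so at most the scale needs confirming.
- **That a percentile interval is planned.** No interval type is named.

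**Conclusion.** The point holds at moderate size. In an institution-randomised trial, the cost-effectiveness text accounts for repeated measurements within workers but names institution neither as a model level nor as the resampling unit. If workers are resampled, the effect standard error is too small by a factor of about 1.13 to 1.20 at the protocol's ICC, and the correct ICER interval is roughly 1.04 to 1.24 times as wide as the one reported.

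The ICER range rests on assumptions that the protocol does not supply: a cost coefficient of variation of 30%, cost ICCs from 0.05 to 1, an even split of 7 institutions per arm, and percentile intervals. Higher ICCs would widen the gap. The scale of the denominator is a matter for confirmation, and the difficulty of a ratio interval near a zero effect is a foreseeable risk. Neither is a demonstrated error.

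**What to change.** In the Statistical analysis section:

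1. Include institution as a level in the models for effectiveness and cost-effectiveness, beside repeated measurements within worker.
2. State that the bootstrap resamples whole institutions within arm and keeps each worker's cost and effect paired.
3. Confirm that the ICER denominator is MVPA work time, as the Economic evaluation section says, and back-transform to minutes if an ilr is modelled.
4. Report incremental net benefit or an acceptability curve alongside the ICER, so that the result can still be read if resampled effect differences cross zero.

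The cost is a few sentences, a few lines of code and a somewhat wider interval. Recruitment, data collection and the intervention are unaffected.
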